**Figure 1 F1:**
[figure not shown]
Subject eligibility criteria.

### Subject eligibility criteria

2.2

People of both sexes, over 18 years old, with good visual acuity, healthy, and who do not need correctional lenses, such as glasses, will be eligible to form Group i. The Group ii will be constituted by people, also over 18 years of age, both genders, with VI or blindness, with good general health, and without other physical and mental disabilities. In this context, those who present visual acuity better than 20/30 in at least 1 eye will be admitted as participant of Group i, without VI. A 2nd group with VI (Group ii), will include individuals with visual acuity less than 20/70 and greater than 20/400 in the best eye; as blind people with visual acuity worse than 20/400, finger counts at 1 m and with lack of light perception in the best eye, according to criteria of the World Health Organization.^[13]^

Individuals who do not comply the clinical criteria described or refused to participate or continue in the survey will be excluded.

Volunteers will be instructed for not drinking alcohol and/or caffeine within 24 hours prior to the intervention.

### Expected risks

2.3

Risks are minimal. If patients feel uncomfortable during evaluation sessions, they can withdraw the research at any time.

### Expected benefits

2.4

Provide scientific information from comparative assessment between the groups, through the analysis of HRV during the proposed tasks.

Demonstrate ANS reactions in different situations with individuals without visual disorder and individuals with VI.

### Intervention

2.5

Liao et al^[14]^ studied 2 groups with 20 patients each, performing a 30-minute exercise program of electric bicycle and a 5-minute cooling during the treatment of hemodialysis (HD) in the renal unit. The exercise was performed under supervision of a physician and a nurse specialized in rehabilitation. This protocol was adapted to be carried out with 2 groups of 50 people each. We also modified the time for the accomplishment of activities, they will be developed in 45 minutes, split in 3 periods of 15 minutes each. Times were defined as rest, intervention, and recovery. The execution will be supervised by a researcher, an ophthalmologist, a professional physical educator, a nurse, a student, and a secretary.

Marques et al^[15]^ measured exercise intensity by using the Borg rating of perceived exertion scale. In our study, patients will perform activities without load prescription. In the study by Raimundo et al,^[16]^ the subjects walked on a treadmill for aerobic exercises split into 5 minutes of warm-up and 25 minutes of exercise, reaching 50% to 70% of their maximal HR. Morais et al^[17]^ used in its protocol in patients in HD, aerobic exercise of cyclical movements of the lower limbs with 45% to 60% of intensity of its HR maximum.

Morais et al^[17]^ performed aerobic exercises with a total time of 30 minutes, 3 times a week for 3 months. The subjects were instructed to remain with arms extended normally in the extension of the chair next to the body, accommodated in the best possible way. The lower limbs that were the most active part in the exercise performed a constant rotation (pedals) throughout the aerobic exercise in the mechanical cycle ergometer for lower limbs. Patients will be encouraged to increase their intensity according to individual capacity, respecting the principle of biological individuality.

In our case, in the intervention phase, the activities performed will be sensorial, by handling objects, the motor part consists in walking blindfolded for 5 minutes through the corridors and clinic rooms, and at the end cognitive activities will be performed with pedagogic games. The protocol was modified so that individuals from both groups will be monitored for 45 minutes, divided into 3 times of 15 minutes each. Each phase will be monitored for its HRV and will be called rest-intervention-recovery. The phase with greater intensity will be the intervention, because the time of this phase will be divided in 3 periods of 5 minutes each. In each subphase of 5 minutes, the individuals will perform 3 different activities. The 1st task will be to serve glasses with water and food. Then, the next task will be locomotion through the clinic areas and the last stage activities will be to assembly pedagogical toys (Figs. 2 and 3).

**Figure 2 F2:**
[figure not shown]
Phase 1 protocol steps.

**Figure 3 F3:**
[figure not shown]
Flowchart of phase 2 protocol steps.

### Team work

2.6

The research team will include 2 ophthalmologists, 2 physical educators, a nurse, 2 medical, nurse and physical education academics, and 2 secretaries from the Rio Branco Eye Health Center (Fig. 4).

**Figure 4 F4:**
[figure not shown]
Team work.

### Data collection instruments

2.7

*First phase*: A sheet will be used to collect personal and sociodemographic data, complemented with clinical data according to the execution of medical examinations and interventions in the study participants.

Initially, it is intended to form the Group ii by searching people with VI from the Pedagogical of Support Center CAP-AC database, a public institution that exclusively provides socioeducational support services to low vision patients and the Centro de Saude Ocular (CSO), which is a private clinic of ophthalmologic care in Rio Branco City. Individuals for Group i those without VI who have good visual acuity will be invited from the CSO, seeking to match them as closely as possible with Group ii, regarding gender, age, occupation, etc.

After initial selection, volunteers will be submitted to routine clinical-ophthalmological examination, where aspects of general health will be investigated, as well as medication that may interfere with ANS, among others. Other aspects of eye health, such as visual acuity, corrective lenses, and history of ophthalmic surgery also will be evaluated.

Clinical and ophthalmological examinations that will indicate the study independent variables will be performed at the CSO, which has qualified human resources and medical equipment for anamnesis, visual acuity measurement, ocular pressure measurement, among others, with no costs for participants.

*Second phase*: In this phase, data of HRV will be collected. The protocol will be the same for both groups (Group i and Group ii). It will be divided in 3 moments of 15 minutes each: rest-intervention-recovery. After taking anthropometric measures, the participant of Group i will be given a brief rest in seated position, in a quiet environment, then the systolic, diastolic, and mean BP and HR will be measured to define a baseline condition (rest phase). Then, in the 2nd step or intervention phase, both eyes of the participant will be blindfolded with a sleeping mask that provides maximum occlusion (Fig. 5), remaining with vigilance and companionship.

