**Objective::**

To analyze the blindness stress by monitoring the activity of the ANS in the heart in subjects submitted acutely to low vision and also in subjects with chronic visual deficiency.

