**Method::**

This is a randomized trial experimental study. In this clinical trial, initially, patients will undergo an ophthalmologic medical evaluation, along with monitoring of HR and systolic blood pressure /diastolic blood pressure. Volunteers with normal vision (Group i); and people with VI (Group ii) will be evaluated, all of them inhabitants of Rio Branco City, capital of Acre State, Brazilian Amazon. The intervention will consist of simulating blindness by sealing both eyes of each participant with good eyesight, using a sleep mask and allowing maximum occlusion for 45 minutes, split into 3 periods of 15 minutes each. Still blindfolded, participants will be requested to perform different tasks as walking, serve themselves water and/or cookies, and engaging in playful-pedagogical activity. Identical procedure will be done with the group with VI. The HR will be recorded by the Polar RS800 HR monitor. All findings with a value of *P* < .05 will be considered statistically significant. As a risk measure the odds ratio will be calculated, adjusted, and not adjusted with their respective 95% confidence intervals. The odds ratio = 1 of lowest risk for the outcome of interest will be considered as the base category for each independent variable.

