**Figure 5 F5:**
[figure not shown]
Maximum occlusion.

Intervention phase will be subdivided into 3 times of 5 minutes each to perform 3 different tasks, as follows:

1.First task, the participant still blindfolded will be asked to perform seizure tasks, serving water and/or biscuits on a tray, sitting with the objects placed at the table in front of him.2.Second task is for motor locomotion, such as walking through clinic areas between corridors and rooms.3.Third task will be ludic-pedagogical activities as fitting of different objects according to their mold like a puzzle (Fig. 6).

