**Figure 6 F6:**
[figure not shown]
Educational toys.

At each stage of 5-minute intervention activities, the patient will be monitored for their systolic and diastolic HR and level of blood glucose.

In the 3rd phase called recovery with a duration of 15 minutes, the participants will sit relaxed and resting, continuing to monitor the collection of autonomic cardiac activity through the HRV.

Participants of Group ii, after verifying their anthropometric measures, will be submitted to the same protocol of Group i.

Measurements include systolic blood pressure, DBP, mean arterial pressure, HR, and blood glucose level.

The HR monitoring for further analysis of HRV will be obtained by an HR receptor RS800CX, Polar Electro, Finland. This device was validated to locate the heart beat for HRV analysis (Fig. 7). At the appropriate moment for collection during the estimated 45 minutes of evaluation, the strap will be placed on the chest of volunteers and the HR receptor (Fig. 8), which is an equipment previously validated for HR reception, beat and use these data for HRV analysis. The receiver temporarily stores the data that will then be processed on computers.

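### Group i's task-phase response combines mask and tasks, and under either stated mask timing the recordings do not isolate acute vision loss; a short seated masked recording would estimate its effect at rest

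*Protocol article*

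**What the plan says.** The objective in the Abstract is "To analyze the blindness stress by monitoring the activity of the ANS in the heart in subjects submitted acutely to low vision", together with people who have chronic visual deficiency.

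Section 2.7 sets out a session of rest, intervention and recovery, 15 minutes each. Group i sits quietly and baseline values are taken. Then, "in the 2nd step or intervention phase, both eyes of the participant will be blindfolded with a sleeping mask that provides maximum occlusion". On content: "Intervention phase will be subdivided into 3 times of 5 minutes each to perform 3 different tasks". The tasks are serving water or biscuits while seated, walking through the clinic, and a fitting puzzle. In recovery the participants sit and rest while recording continues; the text does not say whether the mask is still on. Group ii "will be submitted to the same protocol of Group i".

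Two other places give a different timing. The Method paragraph of the Abstract speaks of "allowing maximum occlusion for 45 minutes, split into 3 periods of 15 minutes each", and section 3.1 also puts the simulated blindness at 45 minutes, which is the whole session.

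Section 2.4 promises a comparison between the groups "through the analysis of HRV during the proposed tasks". Group i is recruited "seeking to match them as closely as possible with Group ii". Section 2.8 names unpaired tests between groups on initial and final values, and no within-person test.

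**The concern.** Walking, handling objects and solving a puzzle can change heart rate and HRV in a fully sighted person. If the mask goes on in the phase that the tasks fill, the Group i response contains both, and no one supplies the missing condition of tasks done with sight. If the mask is on for all 45 minutes, rest is masked too, and the change from rest to tasks contains no onset of vision loss at all.

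At stake is the acute half of the objective. The trial can describe how sighted people respond to doing tasks in a mask, and can compare them with people who have visual impairment. It cannot say how much of the Group i response comes from losing sight. The sequence of conditions is fixed in this document, and no later analysis plan can recover a condition that was never recorded.

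**Working it through.** The plan states no figure on this point: 50 per group is given without an effect size, SD or power. The check is which effects the recorded conditions can separate, and what the remedy could detect.

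**Inputs.** From section 2.7: three 15-minute phases, with three 5-minute tasks filling the second (3 × 5 = 15). From section 2.1: 50 per group. From section 2.8: 5% significance level. Assumed: two-sided tests and 80% power.

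**Step 1. Group i as planned.** Give each phase mean a baseline, a mask effect, a task effect and an after-effect of the tasks. The rows are rest, intervention and recovery; task is coded (0,1,0) and after-effect (0,0,1).
- Mask in intervention only (0,1,0): rank 3 of 4, mask effect not estimable.
- Mask in intervention and recovery (0,1,1): rank 3 of 4, not estimable.
- Mask for all 45 minutes (1,1,1): rank 3 of 4, not estimable.

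Without the after-effect term, the three timings give rank 2 of 3, 3 of 3 and 2 of 3. So there is one way out: mask on after rest, kept on in recovery, and no after-effect. Recovery minus rest would then estimate the mask effect. The article states neither of the last two conditions.

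**Step 2. Adding Group ii.** Take the mask in the intervention only, a baseline for each group, one common task effect, one common after-effect, and a mask effect for each group: rank 5 of 6. Only the difference between the two mask effects is estimable. If the Group ii mask effect is set to zero, the rank is 5 of 5 and the Group i effect can be estimated. That is plausible for members "with lack of light perception in the best eye". It is not plausible for low-vision members, who lose residual sight under the mask. If the groups also respond differently to the tasks, the Group i effect is lost again (5 of 6).

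As an illustration, suppose the mask has no effect and the task responses differ by 0, 0.1, 0.2 or 0.3 SD (assumed values). A two-sample t test on change with 50 per group is then significant in 5%, 8%, 17% or 32% of trials. Such a result is a real group difference. It is an error only if it is read as a mask effect.

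**Step 3. Adding a seated masked recording before task 1.** There are now four rows: unmasked rest, masked rest, tasks, recovery. The mask is (0,1,1,0) or (0,1,1,1); both give rank 4 of 4, and the mask effect is estimable. There are two limits:
- With a mask-by-task term the rank is 4 of 5, because every task is done masked. The mask effect at rest stays estimable; the mask effect during the tasks does not.
- With a linear time term the rank is 4 of 5, and the mask effect cannot be separated from elapsed time.

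**Step 4. What the recording could detect.** For a paired comparison, (1.960 + 0.842)/√50 = 0.396 SD of the within-person difference. The noncentral t distribution gives 0.404, and 0.427 with 45 usable pairs or 0.454 with 40.

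**The case against.** The strongest reply is that the plan never claims what is criticised. Section 2.8 names comparisons between groups, section 2.4 promises the same, and no test of rest against intervention within Group i is listed. The response to functioning without sight in daily tasks is a legitimate target. This stands in part: the article does not attribute the task-phase change to vision loss alone, and a reader should not infer that it does. But the objective concerns acute deprivation, and no planned contrast isolates it.

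Second, a reader might infer that Group i never sits masked before the tasks. That holds only for the section 2.7 timing. Under the Abstract and section 3.1 they do sit masked, and the missing piece is the unmasked rest. The step figures are not shown and may settle it.

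Third, a masked recovery would already give a seated contrast. That is right if the mask stays on and the tasks leave nothing behind. The first is not stated. The second is doubtful in a phase that directly follows walking and a puzzle.

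Fourth, it is tempting to say that a seated masked recording would fix the attribution problem. It would not: the change from rest to tasks would still mix mask and tasks, and the fixed order brings its own time effect. This objection stands in full, and the remedy is limited accordingly.

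**Conclusion.** The point holds in limited form. Under section 2.7, the Group i task-phase response combines mask and tasks. Under the 45-minute timing, there is no unmasked baseline. Either way the planned recordings do not isolate acute vision loss, except under the section 2.7 onset with the mask kept on in recovery and no after-effect of the tasks. The conflict between section 2.7 and the Abstract and section 3.1 is an error in the document itself.

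A reader might go further and call the comparison with Group ii invalid. The documents do not support that. It remains valid as a contrast of acute with chronic loss in non-randomised, loosely matched groups, and only as that.

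The size of the mixing cannot be given, because the article has no figures on the response to mask or tasks. The rank results assume additive phase effects. The 0.40 SD assumes 50 usable pairs and says nothing about whether an effect of that size exists. This is an inexpensive improvement that should be made before recording starts.

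**What to change.** 1. State one mask timing: mask on after the unmasked seated rest. Say whether it stays on in recovery. Correct the Abstract and section 3.1 to match.
2. In both groups, record 5 minutes seated and masked before task 1, the length of one task segment. Preferably take these from the 15-minute rest.
3. In Group i, compare this recording with the last 5 minutes of unmasked rest by a paired t or Wilcoxon signed-rank test, and report it as the response to vision loss at seated rest. The same difference in Group ii members without light perception is a rough check on elapsed time and mask wearing.
4. Describe the task phase as the combined response to mask and tasks.

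**Cost.** Taken from rest: no added time, staff or equipment, and an unmasked baseline of 10 minutes instead of 15. If added instead, the session becomes 50 minutes: 100 × 5 = 500 minutes, or 8.3 hours in all. In the 8:00 to 12:00 window stated for Group i, 240/45 = 5.3 and 240/50 = 4.8, so whole sessions per morning fall from 5 to 4. Group i then needs 13 mornings (50/4 = 12.5) instead of 10, before set-up time.

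**What remains.** The fixed order leaves elapsed time and anticipation mixed with the mask effect. The effect of vision loss during the tasks stays unidentified without a sighted run of the same tasks. Such a run is optional, since familiarity with the puzzle and corridors could carry over.

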**Figure 5 F5:**
[figure not shown]
Maximum occlusion.

Intervention phase will be subdivided into 3 times of 5 minutes each to perform 3 different tasks, as follows:

1.First task, the participant still blindfolded will be asked to perform seizure tasks, serving water and/or biscuits on a tray, sitting with the objects placed at the table in front of him.2.Second task is for motor locomotion, such as walking through clinic areas between corridors and rooms.3.Third task will be ludic-pedagogical activities as fitting of different objects according to their mold like a puzzle (Fig. 6).

**Figure 6 F6:**
[figure not shown]
Educational toys.

At each stage of 5-minute intervention activities, the patient will be monitored for their systolic and diastolic HR and level of blood glucose.

In the 3rd phase called recovery with a duration of 15 minutes, the participants will sit relaxed and resting, continuing to monitor the collection of autonomic cardiac activity through the HRV.

Participants of Group ii, after verifying their anthropometric measures, will be submitted to the same protocol of Group i.

Measurements include systolic blood pressure, DBP, mean arterial pressure, HR, and blood glucose level.

The HR monitoring for further analysis of HRV will be obtained by an HR receptor RS800CX, Polar Electro, Finland. This device was validated to locate the heart beat for HRV analysis (Fig. 7). At the appropriate moment for collection during the estimated 45 minutes of evaluation, the strap will be placed on the chest of volunteers and the HR receptor (Fig. 8), which is an equipment previously validated for HR reception, beat and use these data for HRV analysis. The receiver temporarily stores the data that will then be processed on computers.

**Figure 7 F7:**
[figure not shown]
RS800CX, Polar Electro, Finland.

**Figure 8 F8:**
[figure not shown]
Placement of the belt on the patient.

The recorded pulses will be directed to a computer through an infrared signal emitting interface for analysis of the HRV by Polar Precision Performance software. For data analysis, after storage in the software, they will be filtered at a moderate intensity for the elimination of ectopic beats and/or noises. The HRV analysis will be performed in time and frequency domain (linear analysis) and also by nonlinear analysis (Fig. 9).

**Figure 9 F9:**
[figure not shown]
Data transfer.

Data collection of intervention in subjects of Group i, temporary deprived of vision, will be performed individually, on working days from 8:00 to 12:00 am, recorded in a standardized sheet (Annex 4). The venues will be discrete and isolated, which could be in the outpatient or recreation/training environment of CAP-AC and the CSO in Rio Branco.

### Data analysis

2.8

Data will be analyzed using the Statistical Package for Social Science, version 22.0. Descriptive analysis will be performed for all variables. Data will be expressed as mean ± standard deviation or median (interquartile range), where appropriate. Sample distribution will be tested with the Shapiro–Wilk test. For comparison of initial and final values between groups, the unpaired Student *t* test for parametric distributions and the Mann–Whitney test for nonparametric distributions will be applied. Statistical significance will be considered at the level of *P* < .05 (or 5%).

As a risk measure, odds ratio will be calculated, adjusted, and not adjusted with their respective 95% confidence intervals. The odds ratio = 1 of lowest risk for the outcome of interest will be considered as the base category for each independent variable.

Statistically significant variables in the univariate analysis will compose the model for the multivariate analysis. In this multivariate analysis, multiple logistic regression will be used (Fig. 10).

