### Type, location, and population of the study

2.1

This study protocol follows the items of the Standard Protocol for Randomized Trials. It is an experimental study, specifically a randomized clinical trial on the autonomic HR modulation response, in which 50 volunteers with normal vision (Group i) and 50 individuals with visual deficiency (Group ii) have attended the Pedagogical Service of Support Center for People with VI (Fig. 1).

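### Section 2.8 tests the groups only at undefined initial and final values; no stated test estimates change from rest to the masked tasks, or compares that change between groups

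*Protocol article*

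**What the plan says.** The objective in the Abstract is "To analyze the blindness stress by monitoring the activity of the ANS in the heart in subjects submitted acutely to low vision", and also in people with chronic visual deficiency. Section 2.4 (Expected benefits) promises a comparison of the groups through HRV while the tasks are done, and adds: "Demonstrate ANS reactions in different situations with individuals without visual disorder and individuals with VI".

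The design gives repeated measurements on each person. Section 2.5 (Intervention) states: "Each phase will be monitored for its HRV and will be called rest-intervention-recovery". Section 2.7 (Data collection instruments) takes seated measurements before the mask "to define a baseline condition (rest phase"), applies the mask at the second step, runs three 5-minute tasks, and ends with 15 minutes of seated recovery. Group ii follows the same protocol. Section 2.1 gives the sizes: "50 volunteers with normal vision (Group i) and 50 individuals with visual deficiency (Group ii").

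Section 2.8 (Data analysis) names one comparison for continuous data: "For comparison of initial and final values between groups, the unpaired Student" t test, with Mann–Whitney as the non-parametric alternative, at the 5% level. It also lists descriptive analysis, odds ratios and a regression step: "In this multivariate analysis, multiple logistic regression will be used". The regression has no named outcome and is tied neither to HRV nor to a phase.

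**The concern.** A reaction is a departure from one's own baseline. Two unpaired tests, one on initial and one on final values, estimate the gap between groups at two moments. They do not estimate how far anyone moved, or whether one group moved further than the other.

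Two errors follow. First, the groups are defined by visual status, and section 2.7 matches them only as closely as possible. Any gap at rest can reappear at the final value without anyone having responded. Second, if initial and final mean rest and recovery, a response that appears during the tasks and fades afterwards leaves no trace in either test. Either way, the stated tests do not address the reactions that section 2.4 sets out to show.

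**Working it through.** **Inputs from the document.** 50 per group (section 2.1); three phases (sections 2.5 and 2.7); 5% level (section 2.8), taken as two-sided because sidedness is not stated. The article gives no SD, effect size, within-person correlation or power calculation, so there is no stated figure to reproduce.

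**Assumptions.** Outcome SD of 1 in each phase, within-person correlation ρ, and the effect sizes shown.

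**1. A resting gap carried forward.** SE of a group difference at one time = √(2/50) = 0.200 SD. With a 0.3 SD gap at rest and no response, the final-value test is centred at 0.30/0.200 = 1.5 SE. P(|Z + 1.5| > 1.96) ≈ 32%. With a 0.5 SD gap it is centred at 2.5 SE, and rejection is about 70%.

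**2. Four scenarios.** 10,000 simulated trials each, ρ = 0.5, recovery back at resting level. Entries are the percentage of trials with P < 0.05.

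| Scenario | Groups at rest | Groups at recovery | Groups at task | Paired, Group i | Paired, Group ii | Group difference in change |
|---|---|---|---|---|---|---|
| Group i falls 0.5 SD in task, Group ii unchanged | 5.4 | 5.1 | 70.2 | 93.5 | 5.2 | 70.0 |
| Both fall 0.5 SD in task | 5.0 | 4.8 | 4.7 | 93.7 | 93.1 | 5.4 |
| No response, Group ii 0.5 SD lower throughout | 69.8 | 69.4 | 70.3 | 4.6 | 4.8 | 4.8 |
| Group i falls 0.5 SD in task, Group ii 0.5 SD lower at rest and unchanged | 70.8 | 70.6 | 4.7 | 93.7 | 4.8 | 69.5 |

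On the rest-and-recovery reading, the stated tests are the first two result columns. They stay at the nominal 5% when there is a response and no resting gap (rows 1 and 2). They reject about 70% of the time when there is a gap and no response (row 3). The third column shows that moving the unpaired test to the task phase is not enough: in row 4 a real difference in response is hidden by the resting gap.

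For row 1 the analytic values over ρ = 0.3 to 0.7 are 85% to 99.5% for the paired test in Group i, and 56% to 90% for the group difference in change.

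**3. Precision of change.** SE of the group difference in change = √(4(1 − ρ)/50):

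- ρ = 0.3: √(2.8/50) = 0.237
- ρ = 0.5: √(2.0/50) = 0.200
- ρ = 0.7: √(1.2/50) = 0.155

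Against 0.200 for one time, change is more precise only when 4(1 − ρ) < 2, that is, ρ > 0.5.

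**4. Other readings of initial and final.** Section 2.7 starts the mask at the intervention phase. The Abstract (Method) and section 3.1 describe 45 minutes of visual deprivation, which would span all three phases. On the 45-minute reading the final value is a masked value, but so is the initial one: there is no sighted baseline, and still no within-person test. If final means the end of the intervention phase, the unpaired test still leaves each person's change unestimated.

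**The case against.** **The terms are open.** A reader might infer that the masked phase is certainly never tested. The document does not support that. Initial and final are undefined, the occlusion period is stated in two ways, and the flowcharts are not shown; final could be a masked value. What stands on every reading is that no within-person change is tested. A generous reader might take the sentence to mean group differences in change scores. The text does not say so, and change from rest to recovery would still pass over the tasks.

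**The article is condensed, and section 2.8 contains more than this test.** The sentence covers continuous variables in general and does not name HRV, and a fuller analysis plan may exist. But the article does not leave the comparison open: it fixes a test that does not fit the aim in section 2.4. The logistic regression cannot fill the gap without an outcome.

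**Comparing groups is itself an aim.** True. The fault lies in the timing of the comparison and the missing analysis of change.

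**A resting gap would be visible.** A reader might infer that it would pass unnoticed. In fact the same sentence compares initial values, and matching may narrow the gap. Both points soften the harm. But two separate tests do not combine into an estimate of change: a gap that misses significance at rest and reaches it later would look like a response.

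**Change scores may cost precision.** This stands for ρ below 0.5, as shown above. The case for analysing change rests on answering the right question, not on guaranteed efficiency.

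**Conclusion.** The point holds in this form: section 2.8 names an unpaired group comparison at two undefined moments, and nothing it states estimates the change from rest to the masked-task phase within a person or compares that change between groups. This conclusion follows from the design and does not depend on the figures.

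The size is illustrative. With 50 per group, SD 1 and no response, a carried-over gap of 0.3 SD gives about 32% rejection at the final value, and 0.5 SD about 70%. A 0.5 SD fall in Group i confined to the tasks is detected at about the nominal 5% by tests at rest and recovery, against about 94% for a paired test in that group (ρ = 0.5). The gaps, falls and correlations are all assumed.

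A reader might infer that the right analysis would show what blindfolding alone does to HRV. It would not. Rest is seated and quiet; the intervention phase adds the mask, serving, walking and puzzles together, and no sighted-task condition is described.

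**What to change.** Rewrite the comparison sentence in section 2.8 so that it:

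1. defines the rest, intervention and recovery values of each HRV index over comparable windows;
2. makes the main analysis a repeated-measures or mixed model with group, phase and group-by-phase terms, reporting the rest-to-intervention change in each group and the difference between those changes. Paired contrasts within each group plus a between-group test of the change would also do;
3. transforms only those HRV indices that need it;
4. keeps the unpaired t or Mann–Whitney test to describe resting differences;
5. states that the contrast measures the response to the masked-task phase as a whole, and that change is more precise than a single-time comparison only if the within-person correlation exceeds 0.5.

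The Abstract, section 2.7 and section 3.1 must be reconciled on when the mask is worn, because the meaning of the rest-to-intervention contrast depends on it. If rest were also masked, the contrast would reflect the tasks and not the loss of vision.

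The cost is analysis wording and that reconciliation. HRV is already planned for every phase, so no new data are needed.
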